2b	Interactions with representatives from care organizations during peer education sessions help migrant families overcome distrust and unfamiliarity. These foster increased trust and willingness to seek help from the Dutch healthcare system.	Interviews, observations
3a	Peer education and informational support enhance migrant families’ awareness of available healthcare options. This improves accessibility and fostering better utilization of support services.	Interviews, observations
3b	Ambassadors identify informal caregivers and refer them for tailored follow-up support. This follow-up equips them with the skills and support needed to manage caregiving responsibilities and burdens effectively.	Interviews
4a	Trusted peers (i.e., ambassadors) with strong community ties recruit participants and create a safe, reassuring environment. This increases participation in mental health support programs, despite stigma or mistrust.	Interviews, questionnaire
4b	Participants share knowledge and personal stories with their intervention groups and with their communities. This reduces stigma and spreading understanding about mental health and caregiving.	Interviews, questionnaire, observations
4c	From an organizational perspective, flexibility in adapting training content, communication, and support to cultural and practical needs is needed. This enables inclusive participation and enhances access to information and care for migrant families.	Interviews, observations

**Table 2 tab2:** Overview of data collection methods, CMO-configurations, sample size, frequency, and purpose in realist evaluation.

Method	CMO-configuration	Sample size/frequency	Purpose in realist evaluation
Interviews with ambassadors, semi-structured	1a, 1b, 2a, 2b, 3a, 3b, 4a, 4b, 4c	*n* = 10	Understanding ambassador’s perspectives on CMO-relationships
Interviews with participants, semi-structured	1a, 1b, 2a, 2b, 3a, 3b, 4a, 4b, 4c	2 per ambassador, total *n* = 20	Exploring firsthand experiences of short-term outcomes and factors that influenced these changes
Observations	1a, 1b, 2a, 2b, 3a, 4b, 4c	1–2 per group	Capturing real-time behaviors of ambassadors and participants and context
Post-intervention questionnaire	1a, 1b, 4a, 4b	Approx. *n* = 100 (10 ambassadors, ~10 participants each, varying)	Identifying patterns and insights from participants to support interpretation of qualitative findings

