#### Questionnaire

3.2.4

The quantitative component of this study is of exploratory nature and involves the use of a post-intervention questionnaire conducted among participants of the peer education sessions. It aims to capture differences between participant groups, and it will collect insights into the context and mechanisms related to social support, perceived stigma, group composition, and group dynamics (see Tables 1, 2).

All Phase 2 participants are asked to complete the questionnaire at the end of the final third session. Based on advice of the coordinating organizations, we address practical challenges associated with the target group, such as expected language barriers, diverse backgrounds, and varying literacy levels, the questionnaire was simplified to a maximum B2-level in Dutch. We minimized the number of questions and made answer options straightforward (e.g., yes/sometimes/no) to avoid confusion.

At the end of the third session, the attending researcher distributes paper questionnaires and explains the study’s goal, questionnaire, and informed consent, and instructs participants to complete them individually. In groups where participants do not understand Dutch, a research assistant fluent in the group’s language translates each question aloud, one at a time, for the entire group. This approach allows participants to listen to the translation and fill in their responses individually.

Rather than relying on pre-validated questionnaires, the items were constructed based on theoretical concepts from our CMO-configurations. The questionnaire starts with demographic questions (i.e., age, gender, country of birth of the participant and their parents), and questions related to caregiving responsibilities (i.e., frequency and care recipient). It is followed by section on group composition (specifying familiarity and relationships with group members and ambassador prior to the intervention), social support mechanisms (inspired by Cohen and Wills (40)), and mental health taboos and group dynamics. Lastly, an open-ended section allows participants to share lessons or insights gained during the intervention. Table 3 provides an overview of the themes and items, with the full questionnaire available in Supplementary material III.

**Table 3 tab3:** Overview of questionnaire themes, items and example questions.

Questionnaire themes	Number of items	Examples of items and answer options

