#### Quantitative data: questionnaire

3.3.2

Quantitative data from the post-intervention questionnaire will be analyzed using SPSS [Version 29.0.0.0; (44)] to examine differences across intervention groups and assess the potential influence of contextual factors on perceived mechanisms and outcomes. Based on the initial program theory, we expect differences between groups (i.e., whether participants knew each other or their ambassador beforehand and the cultural homogeneity of the group), which may influence social support and group dynamics (such as sharing personal experiences with caregiving and/or mental illness and perceptions of taboo). To explore these potential mechanisms within our program theory, we will conduct crosstabulations of these independent and dependent variables, supplemented by chi-square tests to assess the statistical significance of observed differences.

Based on previous studies on peer education with migrants [e.g., (45, 46)], we estimate an effect size of 0.4. Using a power analysis in R (47) with the pwr package (48) we expect to need around 60 completed surveys to achieve sufficient power. Given that we anticipate collecting around 8–12 questionnaires per intervention group, totalling approximately 80–100 questionnaires, we expect to have adequate power for our questionnaire analysis.

Missing data will be included in the analyses as is, unless responses to other questions suggest that the omission can be reasonably filled in based on available information. In such cases, missing responses may be assessed using other relevant data from the same participant. All decisions regarding missing data will be reported transparently in the final analysis.

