#### Data triangulation

3.3.3

The data triangulation process will integrate findings from the interviews, observations, and post-intervention questionnaires. Firstly, we will identify patterns where different findings from different data sources align, confirming the validity of specific CMO-configurations from our initial program theory. Discrepancies will be explored, by analyzing the inconsistencies between data sources to understand the variations in context, mechanisms, or outcomes.

The logbook that was kept by researcher MH will serve as a tool to help identify explanations of discrepancies between sources, by offering rationale behind actions and decisions, as well as personal reflections of the study process.

Inspired by Rees (49), a synthesis matrix will be developed to systematically map findings from all sources to the initial CMO-configurations. This matrix will be organized around the four overarching themes from our initial program theory (See Figure 3). Under each theme, the relevant CMO-configurations will be listed, along with associated concepts from the program theory. Data from the interviews, observations and post-intervention questionnaires will be aligned with these themes, allowing for identification of new or modified CMO-configurations, where applicable. This will ensure a structured approach to integrate qualitative and quantitative findings and provide an overview of how data supports or challenges the initial program theory.

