#### Refinement of the program theory

3.3.4

Insights gained from the integrated data will guide the iterative refinement of the program theory. This process starts with evaluating the existing CMO-configurations of the initial program theory based on the triangulated evidence. If the findings indicate that certain configurations are only partially supported or not confirmed, they will be adjusted accordingly. Additionally, if the data reveals previously unconsidered mechanisms or contextual factors, new CMO-configurations will be developed and integrated into the program theory.

The first author (MH) leads the refinement process, while the co-authors provide feedback and discuss discrepancies. We will mitigate potential bias caused by our positionalities – i.e., our backgrounds and perspectives - through regular discussions within the research team. Additionally, throughout the project, regular meetings are held with the TANM’s coordinating organizations to discuss the progress and research design, review the preliminary results, and adjust accordingly.

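### The exploratory questionnaire is judged by chi-square significance alone, so the synthesis cannot separate 'no difference' from 'too little data'; percentage differences with intervals that allow for ambassador group would

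*Protocol article*

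**What the plan says.** Section 3.2.4 of the protocol article sets the status of the questionnaire: "The quantitative component of this study is of exploratory nature". Table 2 gives its purpose: "Identifying patterns and insights from participants to support interpretation of qualitative findings". It links the questionnaire to configurations 1a, 1b, 4a and 4b.

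Section 3.3.2 plans crosstabulations of context factors (prior acquaintance with other participants or the ambassador, and cultural homogeneity of the group) against social support and group dynamics, "supplemented by chi-square tests to assess the statistical significance of observed differences". On numbers it says "we estimate an effect size of 0.4" and "we expect to need around 60 completed surveys to achieve sufficient power". It expects 8–12 forms per group, "totalling approximately 80–100 questionnaires", and concludes that power is adequate.

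Section 3.3.3 maps findings from all sources onto the configurations. On disagreement it says: "Discrepancies will be explored, by analyzing the inconsistencies between data sources to understand the variations in context, mechanisms, or outcomes". Section 3.3.4 provides for configurations that turn out "only partially supported or not confirmed, they will be adjusted accordingly".

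**The concern.** A component meant to show patterns needs the size of a difference and its uncertainty. The crosstabulations give the size but no measure of precision, and the p-value gives neither. A non-significant table can mean that the groups are alike or that there were too few forms to tell, and nothing in sections 3.3.2 to 3.3.4 separates the two.

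The later steps make this matter. Disagreement between sources is to be understood through variation in context, mechanisms or outcomes; imprecision is not among the explanations named. Configurations that are not confirmed are adjusted. A moderate, real context difference that misses significance could therefore prompt a contextual explanation, or a change to a configuration, that the data do not warrant. Configuration 4a is the most exposed, because Table 1 lists only interviews and the questionnaire for it.

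The statement that power is adequate adds to the risk. It holds for large differences, but may encourage reading any non-significant table as absence of a difference.

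**Working it through.** **Inputs from the article:** effect size 0.4; about 60 forms needed; 80–100 expected; about 10 groups of about 10; example answers yes/sometimes/no.

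**Assumed, because not stated:** 0.4 is Cohen's w; two-sided alpha 0.05; power 80%; a two-level factor by three answers, so df = (2−1)×(3−1) = 2; answer rates near 50%; the splits shown; an intraclass correlation (ICC) of 0.05.

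**1. The plan's own figure.** Power is the probability that a noncentral chi-square with noncentrality N·w² exceeds the 5% critical value. With w = 0.4, df = 2 and 80% power, N = 60.2. This agrees with the stated figure of about 60. (With df = 1, N = 49.1; with df = 3, N = 68.1.)

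**2. What w = 0.4 means.** For two equal halves answering yes or no, w = √[0.5·0.5·(p1−p2)²/(p̄(1−p̄))]. For 30% v 70%, w = √(0.25·0.16/0.25) = 0.40, a 40-point gap. For 40% v 60%, w = √(0.25·0.04/0.25) = 0.20, a 20-point gap.

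**3. Power of the planned 2×3 test, independent answers.**

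| True w | N = 80 | N = 100 |
|---|---|---|
| 0.4 | 90.3% | 95.7% |
| 0.3 | 66.9% | 77.1% |
| 0.2 | 34.1% | 41.5% |

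At w = 0.2 the test is therefore non-significant in 58.5–65.9% of studies.

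**4. A 20-point difference on one yes/no split (60% v 40%).** Power is Φ[(0.20 − 1.96·SE0)/SE1], where SE0 = √[p̄(1−p̄)(1/n1+1/n2)] and SE1 = √[0.24(1/n1+1/n2)]. For 40/40, SE0 = 0.1118 and SE1 = 0.1095, so power = Φ(−0.17) = 0.43. The half-width is 1.96·√[0.25(1/n1+1/n2)], at 50% rates.

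| Split | Non-significant | 95% half-width (points) |
|---|---|---|
| 50/50 | 48% | 19.6 |
| 40/40 | 57% | 21.9 |
| 80/20 | 64% | 24.5 |
| 60/20 | 66% | 25.3 |
| 70/10 | not computed | 33.1 |

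**5. Clustering.** For a factor shared by a whole group, the design effect is 1 + (10−1)·0.05 = 1.45, so 80 and 100 forms carry the information of 55.2 and 69.0. With df = 2, power at w = 0.4 falls to 76.2% and 85.4%. At w = 0.2 it falls to 24.5% and 29.8%, so 75.5% and 70.2% of tests are non-significant. A factor that varies within groups, such as prior acquaintance, may be affected less.

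**6. What an interval would show.** With observed rates of 40% and 60%, the difference is +20 points, with 95% interval −1.5 to +41.5 at 40/40 and +0.8 to +39.2 at 50/50. The two tables carry nearly the same evidence but fall on opposite sides of the significance line. The intervals make that visible.

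**The case against.** The strongest objection is that the harm is not written in the plan. A reader might infer that non-significant tests will be entered as 'no difference'. No section says so. The crosstabulations are the main analysis and the chi-square test supplements them, so the percentages will be visible. Discrepancies are to be explored, co-authors discuss them, and a focus group reviews the theory. Every questionnaire-linked configuration also rests on interviews, and 1a, 1b and 4b on observations as well. This stands, and it limits the point to a gap in the rule.

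A second objection is that the 20-point case is half the plan's effect size. This also stands. The figures do not show a study that is underpowered on its own terms: at w = 0.4 and with independent answers, 4–10% of tests would miss. Yet w = 0.4 is a 40-point gap in a balanced yes/no table, and an exploratory survey may well meet smaller ones.

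A third is that a journal article need not name every reporting detail, and a fuller plan might include intervals. That would be an answer if the point were only a missing detail. But the article does state a method, unadjusted significance on clustered forms, and how results feed the theory. Both can be improved as stated.

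**Conclusion.** The point holds in a limited form. Chi-square significance is the only inferential quantity named, and the synthesis has no way to mark a result as imprecise. Large differences will usually be detected: power is about 90–96% at w = 0.4, or about 76–85% for a group-level factor under the assumed ICC of 0.05. Differences of about 20 points would be non-significant in roughly half to two thirds of tests with independent answers, and in about 70–75% under that ICC. They could then be misread as lack of support for 1a, 1b, 4a or 4b.

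The documents do not support saying that such results will be recorded as 'no difference', or that a configuration would be changed because of one test. The sizes rest on the assumed alpha, effect metric, degrees of freedom, answer rates, splits and ICC. The consequence is modest, because the questionnaire plays a supporting role, but the remedy is cheap enough to be worth adopting.

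**What to change.** **Section 3.3.2.** For each comparison, report the difference in the percentage giving a pre-stated answer (for example 'yes' against 'sometimes' or 'no') with a 95% confidence interval that allows for ambassador group. Show the full three-category table beside it and keep p-values secondary. For group-level factors such as cultural homogeneity, base the interval on variation between groups; comparing two sets of group percentages from 10 groups leaves 10 − 2 = 8 degrees of freedom.

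**Section 3.3.3.** State the entry rule for the matrix:
- Supports or contradicts: the interval lies wholly on one side of zero.
- No important difference: the interval covers zero but excludes a difference of interest stated in advance.
- Inconclusive: any other result. It is not treated as a discrepancy or as a configuration that was not confirmed.

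**Cost.** No new data are needed: some extra output, a choice of interval method for few groups, and advance decisions on the answer and the difference of interest. Several results will be labelled inconclusive. With half-widths of about 20 points or more at rates near 50%, differences smaller than that cannot be ruled out in both directions. That reflects what 80–100 forms can show. Reducing three answers to two loses some detail, which is why the full table should stay.

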#### Data triangulation

3.3.3

The data triangulation process will integrate findings from the interviews, observations, and post-intervention questionnaires. Firstly, we will identify patterns where different findings from different data sources align, confirming the validity of specific CMO-configurations from our initial program theory. Discrepancies will be explored, by analyzing the inconsistencies between data sources to understand the variations in context, mechanisms, or outcomes.

The logbook that was kept by researcher MH will serve as a tool to help identify explanations of discrepancies between sources, by offering rationale behind actions and decisions, as well as personal reflections of the study process.

Inspired by Rees (49), a synthesis matrix will be developed to systematically map findings from all sources to the initial CMO-configurations. This matrix will be organized around the four overarching themes from our initial program theory (See Figure 3). Under each theme, the relevant CMO-configurations will be listed, along with associated concepts from the program theory. Data from the interviews, observations and post-intervention questionnaires will be aligned with these themes, allowing for identification of new or modified CMO-configurations, where applicable. This will ensure a structured approach to integrate qualitative and quantitative findings and provide an overview of how data supports or challenges the initial program theory.

#### Refinement of the program theory

3.3.4

Insights gained from the integrated data will guide the iterative refinement of the program theory. This process starts with evaluating the existing CMO-configurations of the initial program theory based on the triangulated evidence. If the findings indicate that certain configurations are only partially supported or not confirmed, they will be adjusted accordingly. Additionally, if the data reveals previously unconsidered mechanisms or contextual factors, new CMO-configurations will be developed and integrated into the program theory.

The first author (MH) leads the refinement process, while the co-authors provide feedback and discuss discrepancies. We will mitigate potential bias caused by our positionalities – i.e., our backgrounds and perspectives - through regular discussions within the research team. Additionally, throughout the project, regular meetings are held with the TANM’s coordinating organizations to discuss the progress and research design, review the preliminary results, and adjust accordingly.

### Phase 4: final validation of the program theory and evaluative synthesis

3.4

The adjusted program theory (Phase 3) will be subjected to a validation process to ensure its relevance and credibility. The theory will be validated in a focus group with the members of t TANM’s coordinating organizations. Feedback and information received during the focus group could lead to one last round of refinement, before reaching the final program theory of TANM. Once the program theory is finalized, we can answer our research questions concerning the perceptions of a successful change in TANM’s short-term outcomes. The process is concluded with an evaluative synthesis of TANM, that assesses whether it achieves it outcomes and which factors influence its success.

## Discussion

4

While previous studies have explored experiences of informal caregivers with a migration background [e.g., (50, 51)] and the stigma surrounding mental illness within migrant communities [e.g., (52–54)], this study will build on that foundation by evaluating an intervention that is aimed at supporting informal caregivers with a migration background who care for a loved one with a mental illness. This protocol shows how we plan to investigate how, why, for whom and under what circumstances TANM produces its intended outcomes.

This protocol employs a RE approach, which is suitable for evaluating interventions that are dynamic, culturally sensitive and context-dependent – like TANM. Unlike traditional randomized experiments, which may not capture the complexity or nuances of real-world settings, RE allows for the consideration of variations in context and experiences as integral to understanding outcomes (27, 55). Its flexibility helps to overcome challenges such as language barriers (35). This makes it a fitting approach for evaluating culturally sensitive interventions like TANM. RE extend qualitative insights to broader patterns by linking context, mechanisms and outcomes, making it more useful for informing policy and practice (27, 55) – which is ultimately the goal of our evaluation of TANM.

However, the flexibility of RE also presents challenges, such as the lack of clear methodological guidance (56). To address this, we employed a mixed-methods approach (35) and multiple data sources for triangulation. Additionally, while RE often uses arrows within program theories, they do not always establish universal causality. Depending on the selection of methods applied in a RE, causality is not necessarily implied. Instead of aiming for universally applicable explanations, REs develop so-called “middle-range” theory – explanations that are specific enough to be useful in practice but broad enough to apply beyond a single case. These theories link empirical findings to hypotheses about how an intervention works, helping to guide future research and program implementation, rather than providing definitive conclusions (56). This study’s program theory will serve as a foundation for future research on culturally sensitive caregiver interventions, such as longitudinal studies assessing long-term impacts or comparative research across different cultural contexts to explore their influence on outcomes.

Our RE approach aligns with its growing use in health system research, particularly in transdisciplinary collaborations. Similar to previous studies [e.g., (57, 58)] we primarily employ qualitative and exploratory methods to evaluate TANM. By sharing the lessons learned from implementing this protocol, we aim to inform the design and evaluation of culturally tailored interventions in integrated healthcare, particularly in reaching underserved and hard-to-reach populations (5, 20).

